## Abstract

**Background:**

The desire to be at home is one of the most important needs of patients with advanced, incurable cancers. However, palliative cancer patients may require inpatient hospital care for medical reasons. Virtual reality (VR) could provide an approximation to the individuals’ home environment.

**Methods:**

The project consists of 3 parts. All parts are supported by the patient advisory board. In the 1st part of the project, we interview patients, relatives, and the patient advisory board about their wishes and concerns regarding the project. In the 2nd part of the project, patients are offered to view 360° VR videos of their choice (their home, relatives, others if applicable). Effects and side-effects of the intervention are assessed with validated instruments (MIDOS, MDBF, SSQ, SPES). Diagnosis, treatment adherence, medication, and vegetative functionality is determined from the medical records of the patients. In the 3rd part of the project, the results of the study will be discussed with patients, relatives, health care professionals and the patient advisory board regarding implementation.

**Discussion:**

This study is the first to investigate whether individualized VR videos have additional benefits over generic VR nature videos on symptom relief, well-being, treatment satisfaction, and adherence in patients with palliative cancer care. A strength of the study is that we can incorporate the results of each part of the project into the subsequent project parts. However, the generalizability might be limited as this is a single-centred study.

**Trial registration:**

Registered at German Clinical Trials Register (Deutsches Register Klinischer Studien; DRKS); registration number: DRKS00032172; registration date: 11/07/2023 https://drks.de/search/de/trial/DRKS00032172.

**Supplementary Information:**

The online version contains supplementary material available at 10.1186/s12904-023-01297-z.

## Background

To be at home is one of the most important desires of patients with advanced, incurable cancer [1, 2]. Therefore, spending as much time as possible at home is gaining importance in palliative cancer care [3, 4]. Patients express a desire for moments of normalcy in which they are allowed to be a person and do not feel reduced to their patient role [5]. Such normalcy may be facilitated by the familiar home environment.

Still, palliative cancer patients may need inpatient hospital care for medical reasons. In this case, virtual reality (VR) could provide a bridge to the individual home environment, when patients view their home in VR and ideally “feel at home”. In VR, immersion refers to the feeling of being in a different world [6]. In the intended application of our study, this world is the places the patients’ desire. VR applications distract from visual and auditory stimuli that can cause anxiety, longing, and other negative feelings, and have a positive effect on symptom relief and well-being [7–11]. For example, patients undergoing chemotherapy reported reduction of anxiety due to altered perception of time, as well as feelings of fun and enjoyment [12, 13]. Cancer patients who view nature images via VR headsets experience less pain and a higher sense of well-being [14]. Here, the nature images are identical for all individuals. Initial research on the potential of personalized VR in palliative care did not show significant results, which was attributed to the limited selection of VR video scenarios [15]. The use of home VR videos could increase the effect of individual images [16, 17], and respond to the desire to feel at home.

The aim of the study is to assess if VR videos with content tailored to the individual palliative cancer inpatient’s desire to be at home are accepted and suitable to improve their quality of life. The specific objectives of the study are:

Exploration of patient and family views about desired content and concerns of a VR intervention, and consultation with the patient advisory committee;Clinical testing of an individualized VR intervention for palliative cancer patients;Patient-and-Public-Involvement (PPI) with patients, families, patient advisory board, and the involved hospital wards for a reciprocal exchange of findings, which will be used for the further implementation.

## Methods

This study is composed of three successive parts that build upon each other, continuously accompanied by the patient advisory board, which is already involved in the writing of the study protocol. Both, qualitative and quantitative methods will be applied.

### Procedure

All eligible persons for the three parts of the project will be informed about the study in general and the particular project part. After informed consent the participants will be interviewed (I, III), or experience the VR videos (II) with outcome assessments before and after the intervention. Results will be discussed with the patient advisory board after each of the project parts to inform the following project part.

### Project part I: PPI on desired content and concerns of a VR intervention

Aim, study design and setting: We conduct semi-structured interviews with inpatients and family members to explore wishes and concerns regarding VR; further, we ask specifically about 360° video recordings of one’s own home and family. The setting are units of the Heidelberg University Hospital that care for palliative cancer patients. In a consultative session with members of the patient advisory board, the contents of the interview will be discussed.

Participants: Palliative cancer patients at Heidelberg University Hospital and their family members are invited to the interview. They are identified by the attending physician of the unit (palliative care, radiotherapy, haematology). Inclusion criteria are age ≥ 18 years; patients or family members of patients diagnosed with an oncological or haematological disease that is not curable or is associated with an uncertain prognosis; capacity to consent. Exclusion criteria for patients include patients, who are in a poor general condition or too stressed to participate in any study as assessed by the health care professionals in charge; cognitive or communication deficits; life expectancy of only a few days. Exclusion criteria for family members include relatives who feel too burdened to participate in a study; cognitive or communication deficits; and being a family member of a dying patient.

Interviews: The semi-structured interview guide includes questions about wishes, concerns, and possible benefits of personalized VR videos in palliative cancer care. To respond to possible emotional distress, further topics and thoughts that complement from the study questions are given space and respect. The informed consent as well as the interview will take approximately 15–20 min. Information regarding the medical condition of participating patients is pseudonymized and transferred to a digital file by persons bound to confidentiality on the basis of the patient file. Patients will be asked for demographic information and length of stay (recorded pseudonymously).

Data analysis: We conduct interviews until there is data saturation in terms of no new information related to the research question [18]. To achieve this, we will continuously reflect in our interdisciplinary working group on the interviewees’ responses throughout the interview phase. We estimate the number of 20 interviews based on previous experiences with these participant groups [19]. The interviews will be audio-recorded, transcribed and analysed (content analysis). The focus points of the interview are set deductively, i.e. theory-guided, and form the framework for the category system in the analysis. The subcategories are developed inductively, i.e. from the interview material [20]. We apply descriptive quantitative methods (frequency distribution, mean, median, interquartile range) to evaluate the sociodemographic variables and data on the medical condition for the description of the purposive sample.

### Project part II: assessment of the experience with the individualized VR-intervention

Aim, study design and setting: In a prospective clinical cohort study, we assess the influence of personalized VR videos on symptoms, well-being, and vegetative functionality. Data will be collected using questionnaires and patient record analysis. First and foremost, we want to ensure patient safety. Thus, the aim is to prove a non-inferiority of the intervention in this vulnerable group and to start with 10 patients at least. Further, we want to observe whether ceiling effects occur in terms of well-being in this patient group, and to match the subjective verbal judgment of the patients regarding well-being after the VR-experience compared to baseline to reflect on the assumption that the minimally clinically important difference for well-being as assessed with the MDBF (Multi Dimensional Well-being Questionnaire) [21] is a 0.5 standard deviation or actually more prior to the sample size calculation for a power of 0.8 with a one sided significance level of 0.05, resp. effect size in a consecutive larger sample [22, 23]. This piloting is important because from our assumption so far the sample size would range between 30 and 130 participants [24, 25].

Participants: The same inclusion and exclusion criteria apply as in project part I.

Intervention: We create personalized VR videos as requested from the patients, probably from the patient’s home or family members. After the videos are created, the patients watch the videos using VR headsets while being cared for in a hospital unit. The videos are edited to a length of about 3–15 min. The patients watch the generic nature video for comparison before or after the personalized video (1:1 randomization). Before and after watching the videos, the patients answer the questionnaires using a tablet computer; support by a trained research assistant is provided to the comfort of the patients. The whole procedure of VR application takes about 20–30 min. If desired, patients can watch the personalized video repeatedly on different days for a maximum duration of 14 days. If patients are interested, they will be provided with the video file.

Questionnaires: Symptom perception (minimal documentation system, MIDOS) [26], well-being (MDBF Multidimensional Well-Being Questionnaire) [21], subjective benefit of VR videos (2 self-developed items), cybersickness (SSQ Simulator Sickness Questionnaire) [27], presence experience (SPES Spatial Presence Experience Scale) [28].

In addition to interviewing patients after viewing VR videos, information on disease, treatment adherence, pain medication, and vegetative functionality will be collected from patient records to avoid further, potentially burdensome physical examinations during study participation.

Data analysis: The analysis is performed with the total data set reflecting the intention-to-treat principle. Descriptive methods are used for the analysis of all collected data (frequency distributions, mean, median, interquartile). For the pre/post comparisons of the outcomes (well-being, symptom perception, treatment experience, treatment adherence, pain medication, autonomic functionality), with well-being as the primary outcome, non-parametric Wilcoxon signed-rank t-tests for repeated measures data are calculated. Analysis is performed using IBM SPSS Statistics and R (r-project.org).

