## Discussion

This study aims to investigate whether individual VR videos provide benefits in terms of symptom relief, well-being, treatment satisfaction, and treatment adherence in palliative cancer care. The novelty of this project are the individualized VR videos as in previous research with palliative patients only generic videos, such as nature shots, were used.

A further strength of the study is that the patients’ opinions as well as those of the relatives and the patient advisory board are considered, i.e., heavily involving those concerned by the intervention in its development. The combination of qualitative and quantitative method allows to inform the subsequent project parts: In the first part, we start with qualitative interviews to gain an in-depth understanding of the topic. We ask not only about wishes and needs, but also about worries and concerns. The results of the first part enable us to respond with a high degree of flexibility to the needs of the patients in the second part of the study. Moreover, we ensure patient safety when we assess and compare cybersickness, symptoms, and use of medication for symptoms before and after the intervention with no tolerance for a decline of the patient’s subjective wellbeing. The study is designed to implement VR video use tailored to the needs of patients feasible not only under laboratory conditions but in everyday clinical practice.

However, the generalisability of our study results will be limited because we perform a single centre study. Nevertheless, the experiences from the project may inform others who want to adapt the intervention to their site or to other palliative care samples. In terms of the sample, we suspect that particularly highly burdened patients will not participate in the study, although they would like to use the VR intervention outside of a trial. For this reason, we involve relatives and the patient representatives’ experiences and attitudes as a proxy. Whether older patients will be more likely to decline study participation because of restraints towards new technology is an apprehension that could not be clarified in former studies applying VR interventions to older people [29], and we aim to consider the particular needs of vulnerable and old people to operate the VR intervention.

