The NCT funding board reviewed a summary of this study to ensure its aims and objectives, study design and outcome are suited and promising to improve the care of cancer patients. The Institute for Biometrics of the Heidelberg University Hospital reviewed the quantitative data analysis plan and recommended descriptive methods. The anthropologist and research coordinator of the Department of Palliative Care of the Heidelberg University Hospital reviewed the protocol regarding the qualitative methodology and mixed methods approach. Further, three members of the NCT patient advisory board informed the interview guide, the selection of questionnaires, and the sheets for informed consent. They found it important to explore the potential of individualized VR-videos to alleviate the situation of palliative inpatients with cancer. In this context, they welcomed the approach to find out the wishes and concerns of patients and relatives related to the intervention to guide its implementation.

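### Part II sets out to prove non-inferiority, but names no margin and no comparator, and its only test is a pre/post difference test

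*Protocol article*

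**What the plan says.** The aim paragraph of Project part II puts patient safety first and continues: "Thus, the aim is to prove a non-inferiority of the intervention in this vulnerable group and to start with 10 patients at least". It then describes this stage as piloting. One purpose is to check whether the minimally clinically important difference in MDBF well-being "is a 0.5 standard deviation or actually more prior to the sample size calculation". The operating characteristics are stated "for a power of 0.8 with a one sided significance level of 0.05, resp. effect size in a consecutive larger sample", and that later sample is expected to lie between 30 and 130. The 0.5 SD is not called a non-inferiority margin, and the SD it refers to is not specified.

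The data analysis paragraph of Part II provides descriptive statistics for everything collected. For the pre/post comparisons, with well-being as primary outcome, it says "non-parametric Wilcoxon signed-rank t-tests for repeated measures data are calculated". Each patient also watches a generic nature video, in randomised order, as a comparison.

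The Discussion adds that safety will be assessed "with no tolerance for a decline of the patient’s subjective wellbeing". It also reports that the biometrics institute "reviewed the quantitative data analysis plan and recommended descriptive methods".

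**The concern.** A non-inferiority claim needs three things: a reference, a margin, and a rule that rejects a decline as large as the margin. The article states the claim and a test, but the test as described addresses whether there is any change. Failing to detect a change in a small sample says little about whether a relevant decline has been ruled out.

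The other statements do not close the gap. Read as a margin, the zero-tolerance phrase makes non-inferiority the same as superiority over baseline. The reported biometric advice points to description, not proof. Proof of non-inferiority, a difference test, zero tolerance and description cannot all govern one analysis.

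At stake is the first-named purpose of Part II, whose results go on to inform implementation in Part III. An unremarkable pre/post test in a handful of patients could be taken as a demonstration of safety.

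**Working it through.** **Inputs from the article.** At least 10 patients at the start; an important difference of 0.5 SD; one-sided level 0.05 and power 0.8 (both for the later sample); later sample 30 to 130; Wilcoxon signed-rank test on pre/post data.

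**Assumptions.** Normally distributed paired changes; a margin of 0.5 SD, because the article gives none; baseline as reference, because the article names none. SD means the SD of the paired change unless stated otherwise.

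**1. The plan's own figure.** The number 10 has no derivation to reproduce. For the later sample, a paired design with d = 0.5 gives n = ((1.645 + 0.842)/0.5)² = 24.7, so 25. The t-test needs 27, and the Wilcoxon test about 28 (27/0.955) to 31 (27/0.864). The lower end of 30 is therefore consistent with the stated inputs. The upper end of 130 is not fixed by them: in a paired one-sided design it corresponds to an effect of about 0.22 SD.

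**2. Precision at n = 10.** The one-sided 95% limit lies t(0.95; 9)/√10 = 1.833/3.162 = 0.58 SD of change below the mean.

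**3. Power for non-inferiority at n = 10, true change 0.** From the noncentral t distribution with noncentrality margin × √10:

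| Assumed margin (SD of change) | Power at n = 10 (t) | n for 80% power (t) |
|---|---|---|
| 0 | 5% | none |
| 0.2 | 14.5% | 156 |
| 0.3 | 22% | 71 |
| 0.5 | 43% | 27 |
| 0.8 | 75% | 12 |

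At 0.5 SD the exact Wilcoxon test (attained level 0.042) has power of about 38% with 10 patients and about 82% with 28. With a zero margin and no true change, power equals the level, so it is at most 5% at any sample size.

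**4. If 0.5 SD means the SD of the score.** With equal pre and post SDs and correlation r, the SD of change is √(2(1 − r)) score SDs. The margin in SDs of change is then 0.5/√(2(1 − r)):

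| r | Limit at n = 10 (score SD) | Power at n = 10 (t) |
|---|---|---|
| 0.3 | 0.69 | 34% |
| 0.5 | 0.58 | 43% |
| 0.7 | 0.45 | 59.5% |
| 0.8 | 0.37 | 75% |
| 0.9 | 0.26 | 95% |

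The limit equals 0.5 score SD where 0.58 × √(2(1 − r)) = 0.5, that is at r of about 0.63. The article gives no correlation.

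**5. What a non-significant test would hide.** With a true worsening of 0.5 SD of change and n = 10, simulation of the exact signed-rank test gives a non-significant two-sided result in about 71% of pilots. A one-sided test for harm misses it in about 62%.

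**6. The route through superiority.** A significant improvement would exclude a mean decline. At n = 10 the one-sided Wilcoxon test achieves this with probability about 38% if the true gain is 0.5 SD of change, and at most 5% if there is no true change.

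**The case against.** The strongest reply is that the 10 patients are a pilot. The article says "to start with 10 patients at least", calls the stage piloting, and attaches level and power to a later sample whose lower end of 30 already exceeds the 28 needed at a margin of 0.5 SD of change. This stands as far as it goes: a reader might infer that 10 is the final sample for the proof, and the article does not say so. But the same sentence ties the non-inferiority aim to those patients, and a larger sample supplies neither a margin nor a comparator.

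A second reply is that the null value of the signed-rank test is not stated; the same procedure can be run against a shifted null or inverted to a confidence limit, and a condensed article may leave this to a fuller plan. That is fair for the mechanics. It does not settle what margin or reference would be used, and the only margin-like statement, zero tolerance, makes the shift zero. Nor does the article say that a non-significant result will be reported as safe; that is a risk of the wording, not a stated rule.

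Three stronger readings are tempting and not supported:

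- **Zero tolerance as a per-patient rule.** A reader might infer that no single patient may score lower. The article states no per-patient criterion.
- **The limit at n = 10 being wider than the plan's 0.5 SD.** This compares an SD of change with an unspecified SD. On the score scale it holds only for correlations below about 0.63.
- **Ten patients never being enough.** With a margin of 0.8 SD of change power is 75%, and with a margin of 0.5 score SD and correlation 0.9 it is 95%.

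Finally, the biometric advice is only a reported recommendation, and the analysis paragraph largely follows it. It shows tension with the word prove, not a second analysis plan.

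**Conclusion.** The stated aim and the stated analysis of Part II do not match. Following the article as written gives a sound conclusion of no decline only if a significant improvement is shown; a non-significant pre/post test would not support one. Saying that non-inferiority can never be established would go too far, because that one route exists.

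The size of the problem in a 10-patient pilot depends on inputs the article does not give. For a margin of 0.5 SD of change, power is about 43% (t) or 38% (Wilcoxon). For 0.5 score SD it is about 34% to 95% over correlations of 0.3 to 0.9. These figures rest on normal changes, no true change and, for the score scale, equal pre and post SDs. The mismatch between aim and test does not depend on any of these assumptions.

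**What to change.** 1. **First 10 patients.** Restate this stage as descriptive: the estimated change with its confidence interval and the number of patients declining with an exact interval. Make no non-inferiority claim.
2. **Larger sample.** Name the comparator (baseline or nature video) and a justified margin in MDBF points. Conclude non-inferiority only if the lower one-sided 95% limit of the Hodges-Lehmann estimate lies above minus the margin, taking change from baseline or the paired difference between videos according to the comparator chosen. Size the sample for this test, stating whether the SD is that of the score or of the change and, if the score, the assumed correlation.
3. **Discussion.** Reconcile the phrase "with no tolerance for a decline" with the chosen margin.

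The pilot needs only rewording, with no new measurements. The price is a more modest safety claim from the first patients; the size of the larger sample will depend on the margin, for example 27 (t) or about 28 (Wilcoxon) at 0.5 SD of change and 71 (t) at 0.3.

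### As worded, the questionnaires enclose both videos together, so the personalised-versus-generic benefit cannot be identified unless a round between the videos is stated

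*Protocol article*

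**What the plan says.** The Discussion paragraph of the Abstract sets the question: the study is to investigate "whether individualized VR videos have additional benefits over generic VR nature videos". Under Methods, Project part II, Intervention, every patient sees both kinds of video: "The patients watch the generic nature video for comparison before or after the personalized video (1:1 randomization". The next sentence fixes the measurement times: "Before and after watching the videos, the patients answer the questionnaires using a tablet computer". The same paragraph gives two durations: "The videos are edited to a length of about 3–15 min" and "The whole procedure of VR application takes about 20–30 min".

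The other statements on timing have the same two-point form:

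- Methods, Procedure: participants in part II "experience the VR videos (II) with outcome assessments before and after the intervention".
- Project part II, Data analysis: the tests are pre/post comparisons, "with well-being as the primary outcome, non-parametric Wilcoxon signed-rank t-tests for repeated measures data are calculated". No contrast between personalised and generic video is named.
- Main Discussion: the safety comparison of cybersickness, symptoms and symptom medication is again before against after the intervention.

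The article mentions no questionnaire round between the two videos, and excludes none. It does not give the length of the nature video, the interval between the videos or any washout.

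**The concern.** The generic video is there to serve as comparator, and its position is randomised. That design answers its question only if some score can be attributed to one video alone. The measurement sentence comes directly after the sentence that introduces the pair, so its natural referent is the pair. A research assistant who followed it literally would collect two scores per patient, and both order groups would have seen both videos by the second score.

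Two things are at stake. First, the personalised-versus-generic comparison in the Abstract would have no data behind it. Secondly, even the narrower aim of part II, the influence of the personalised video on well-being, would be blurred. A gain, a decline or cybersickness measured around both videos cannot be assigned to either one. A between-video score that was never collected cannot be recovered in the analysis.

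**Working it through.** The plan gives no figure for this contrast, so there is none to reproduce. The check asks whether the contrast can be estimated under each reading of the timing.

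**Notation.** P and G are the mean changes in well-being produced by the personalised and the generic video. PG and GP are the two randomised orders.

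**Literal reading: one score before and one after both videos.** With *s* for any order effect:

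- order PG: expected change = P + G + s
- order GP: expected change = P + G

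The difference between the order groups is s alone. In the columns (P, G, s) the design rows are (1, 1, 1) and (1, 1, 0), which have rank 2. The contrast P − G is the row (1, −1, 0). Adding it raises the rank to 3, so it is not estimable. Without s the rank is 1 and P − G is again not estimable. Neither is P on its own.

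Three effect pairs, in SD units and with s = 0, illustrate this:

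| P | G | Expected change P + G |
|---|---|---|
| 0.5 | 0 | 0.5 |
| 0 | 0.5 | 0.5 |
| 0.25 | 0.25 | 0.5 |

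Simulated mean changes with 200,000 patients per row were 0.498, 0.497 and 0.501. The data cannot tell these cases apart, whether there are 10, 30 or 130 patients.

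**Per-video reading: scores before, between and after.** With π for a period effect and no carry-over:

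- order PG: first change P, second change G + π
- order GP: first change G, second change P + π

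The four rows have rank 3 for three parameters, so P − G is estimable. First minus second change is P − G − π in PG and G − P − π in GP. Half the difference between these is P − G.

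**Carry-over.** Let the first video alter the second change by c(P) in order PG and by c(G) in order GP. Half the difference becomes P − G − [c(P) − c(G)]/2. The between-video score therefore does not remove carry-over, because without a washout it already contains the first video's effect. The first change compared between order groups is P − G with no c term.

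**Session time.** Assume that the nature video is about as long as the personalised one.

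- Short end: 2 × 3 = 6 min, leaving 20 − 6 = 14 to 30 − 6 = 24 min.
- Long end: 2 × 15 = 30 min, leaving 30 − 30 = 0 min of the longer session and 20 − 30 = −10 min of the shorter.

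At the short end three rounds may fit. At the long end not even the undisputed before and after rounds fit. The duration therefore does not decide between the readings. It does show that the article must say what the 20–30 min covers.

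**The case against.** The strongest reply is that the plural noun need not mean the pair. Earlier in the same paragraph it is used of personalised videos across patients, before the nature video is mentioned. The sentence can thus mean before and after each video, and randomising the order for comparison makes sense only on that reading. The Procedure sentence, "with outcome assessments before and after the intervention", is a one-line overview of three project parts and settles little. The article is also condensed, and the full protocol may hold an assessment schedule.

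Much of this stands. A reader might infer that the trial certainly cannot separate the two videos, but the text does not support that: a middle round is unstated, not ruled out. A reader might also infer from the session length that no middle round exists, or that the videos run back to back. The first does not follow from the time sums, and the second is not stated anywhere. Nor should the first-video comparison between order groups be taken for a test of carry-over; it is the treatment estimate that carry-over does not touch.

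The reply does not remove the point. That the design needs per-video scores does not mean the text provides for them. The article is not silent on timing: it states timing several times, always as one before and one after, and the analysis paragraph names no per-video change. This is a stated rule that, taken literally, defeats the stated comparison. It is not a detail left to a longer document.

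**Conclusion.** The point holds conditionally. If the wording is followed literally, the information on personalised minus generic is nil at any sample size, and randomising the order does not help. This conclusion needs no assumption about carry-over, washout or video length. If questionnaires are in fact completed around each video, the contrast is estimable: from all four changes assuming equal or no carry-over, and from the first video alone without that assumption. The article supports both readings and states only the before-and-after form. Because a missing score cannot be repaired afterwards, the timing should be settled before part II data are collected.

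**What to change.** - State three assessments of MDBF, MIDOS and SSQ: before the first video, between the videos and after the second. Give SPES after each video.
- Name the comparison: per-video changes within patients, personalised against generic, allowing for period.
- Report the first-video change between the randomised order groups as the comparison free of carry-over.
- Acknowledge that without a washout the between-video score contains the first video's effect and does not remove carry-over.
- State whether the 20–30 min includes questionnaires and both viewings, give the length of the nature video, and reconcile the total with the video lengths and three questionnaire rounds.

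The cost is one more short questionnaire round for patients who may be frail, and a restated session time in the protocol and patient information. If a middle round is already intended, only the wording changes.
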